**Fig. 5 Fig5:**
[figure not shown]
Example page from brochure template

#### Pretest of the intervention material

Both versions of the intervention were pretested in order to be able to adapt the content. There were two phases during the pretest. In the first phase, tentative drafts of the intervention materials were shown to women from the target group. The women were asked to evaluate draft advice messages, pictures used in the brochures and the layout of the brochures. A qualitative approach was applied by asking the participants to read through the material, while an interviewer asked questions about the likability, readability, attractiveness and usability of the material. During the second phase of the pretest, the intervention delivery process was assessed. Five Dutch women (mean age 55.8 years) and 18 Turkish women (mean age 41.8 years) filled out the baseline questionnaire and received the first two brochures, which were tailored to their answers on the questionnaire. The participants were asked to give feedback on the brochures as a whole by means of a structured questionnaire asking, for instance, about the degree of personal relevance and individualization of the brochures.

Generally, the intervention material was appreciated by the women. They perceived the texts as readable and interesting and both the length of the messages and the layout were appropriate. The material was perceived as personally relevant and the women said that they would use the advice given in the brochures. General critique points were that the pictures of the role models and vegetables could be improved by making them more precise. A few women said that the information in the brochure was not new to them and one woman would not use the agenda that is provided with the brochure because it would take her too much time. The Turkish women criticized strongly the way the brochures for the EI-tailoring intervention referred to religious rules, which they thought was offensive and irrelevant. Furthermore, they did not like the fact that all of the role models in the picture were wearing a headscarf in the traditional EI category. Therefore, we decided to remove parts of the text and images that referred to religious rules and Islam from the EI-tailoring intervention for the Turkish population.

### Evaluating the interventions

In the fifth and sixth steps of the IM protocol, the implementation and evaluation of the intervention are planned [44]. Before starting implementation efforts, we will evaluate the intervention’s effectiveness.

#### Design, participants and procedure

The two versions of the intervention will be evaluated in a randomized controlled trial with three study groups: traditional tailoring, EI-tailoring and a control group receiving generic, nontailored information. The primary outcome measures are fruit, vegetable and snack consumption, and PA. Mediating variables are awareness of one’s own behavior, attitude, self-efficacy, social support and intention towards more fruit, vegetable and snack consumption and PA. A process evaluation will be conducted at three-month follow-up, assessing the self-reported use, relevance and appreciation of the intervention.

It is hypothesized that both interventions are more effective than the control intervention and that the EI-tailoring intervention will reach higher effect sizes and higher acceptance among the target group than the traditional tailoring intervention. The required number of participants for this study is 1000, of which 500 should be of Dutch origin, 250 of Turkish origin and 250 of Moroccan origin. To be able to detect a small intervention effect (ES = 0.3), with a power of 0.8 and a significance level of p < .05, 250 people are needed in each study condition, which adds up to 750 participants in total. Taking a dropout rate of 10 % at each measurement moment into account, 1000 participants have to be included at baseline.

The target group consists of lower-educated adult women (lower vocational level or below), who are aged between 20 and 65 years, and who are of Dutch, Turkish or Moroccan origin. We use the standard definition for origin as described by Statistics Netherlands [68]. Participants with an insufficient knowledge of the Dutch language, or a health condition that may restrict their eating and/or PA behavior, are excluded from the study. Moreover, women whose baseline assessment shows that they do not perform the risk behaviors will be excluded from the study.

We use active recruitment strategies by approaching participants directly. In addition, passive strategies are applied by sending, for instance, e-mails to potential participants. Table 5 provides an overview of all recruitment strategies. The paper questionnaires will be sent to the participants’ home address or handed out to them in person. After the baseline measurement, participants will be pre-stratified based on their origin. The participants will then be randomly assigned to one of the three intervention groups by means of a computer-determined sequence. The intervention material is generated by means of the TailorBuilder program. The brochures will be sent or handed out to the participants. The participants will be rewarded with gift vouchers worth €20.

**Table 5 Tab5:** Recruitment strategies

Active recruitment strategies
Approaching participants via general practitioners or nurse practitioners
Approaching participants at events, markets and fairs
Approaching participants at public venues, such as community centers and mosques
Approaching participants via foundations or social work organizations
Approaching participants via stakeholders from the target group
Approaching participants via the public health service
Word-to-mouth distribution via participants (snow ball method)
Approaching participants via research/recruitment institutes (active approach by Turkish and Moroccan recruiters)
Passive recruitment strategies
Call for participation via public media -Websites -Magazines -Facebook
Call for participation via companies via e-mail -Cleaning companies -Nursing companies -Home care companies
Call for participation via research panels from research/recruitment institutes via e-mail

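### The sample size sentence does not agree with itself: ES 0.3, power 0.8 and p < .05 call for about 175 women per condition, not 250, and the gap is on the conservative side

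*Protocol article*

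**What the plan says.** The calculation is in the protocol article, section Design, participants and procedure.

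- **Design:** "a randomized controlled trial with three study groups: traditional tailoring, EI-tailoring and a control group".
- **Primary outcomes:** "The primary outcome measures are fruit, vegetable and snack consumption, and PA", so four.
- **Effect size:** the sentence opens with "To be able to detect a small intervention effect (ES = 0.3". The metric of this effect size is not defined.
- **Power, significance level and number per condition:** "with a power of 0.8 and a significance level of p < .05, 250 people are needed in each study condition". The number of sides is not given, and no adjustment for several tests is mentioned.
- **Total before dropout:** "250 people are needed in each study condition, which adds up to 750 participants in total".
- **Dropout:** a separate, later step. "Taking a dropout rate of 10 % at each measurement moment into account, 1000 participants have to be included at baseline".

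The section Statistical analysis plans linear and logistic regression on individual women. It names no correction of the significance level and no design effect.

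**The concern.** Effect size, power, significance level and number per condition are tied together: once three are fixed, the fourth follows. Here all four are printed in one sentence, and the usual two-group formula does not connect them.

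What is at stake is the reading of the trial rather than its size. If 250 came from a stricter per-test level, the printed level is not the one the trial was sized on, and testing four primary outcomes at .05 each would drop a correction that had been planned. If .05 was meant, the stated power or the stated detectable effect is wrong. These readings lead to different significance thresholds in the final analysis, so the matter is best settled before results are known.

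**Working it through.** **Inputs.** Effect size d = 0.3, power 0.80, level 0.05, three equal conditions, all from Design, participants and procedure. Assumptions, because the article does not state them: d is a standardized mean difference, the test compares two conditions, and every woman contributes to the outcome.

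**Step 1: try to reproduce 250 from the printed inputs.**

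n per condition = 2(z₁₋α/₂ + z_power)² / d²

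- Two-sided: 2(1.9600 + 0.8416)² / 0.09 = 2 × 7.849 / 0.09 = 174.4, so 175. The exact t-test gives 175.4, so 176.
- One-sided: 2(1.6449 + 0.8416)² / 0.09 = 137.4, so 138. The exact t-test gives 138.1, so 139.
- Three-group analysis of variance at 0.05 and 80% power: 37 per condition at f = 0.3, 144 at f = 0.15, 162 at f = 0.141, 215 at f = 0.122 and 322 at f = 0.10.

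None gives 250. Against the two-sided result, 250/175 = 1.43, so the printed figure is 43% higher. Over three conditions the comparison is 750 with 3 × 175 = 525, or 3 × 176 = 528.

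**Step 2: what 250 per condition delivers at two-sided .05.**

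- Power at d = 0.3: Φ(0.3/√(2/250) − 1.9600) = Φ(3.354 − 1.960) = Φ(1.394) = 0.918 (exact t-test 0.917).
- Detectable d at 80% power: 2.8016 × √(2/250) = 2.8016 × 0.08944 = 0.251.

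**Step 3: which single change leads to about 250?**

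| Change, all else as printed | n per condition |
|---|---|
| d = 0.25 | 252 (exact t-test 253) |
| power 0.92 | 252 |
| two-sided level .05/4 = .0125 | 248 (exact t-test 250) |
| two-sided level .05/2 | 212 |
| two-sided level .05/3 | 233 |
| two-sided level .05/6 | 270 |

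The first three all land within rounding of 250.

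**Step 4: can dropout explain it?** The article applies dropout after the 750, so it should not already be inside the 250. The inflation is also accounted for at that stage: over the three follow-ups (one, three and nine months, section Measurements), 750 × 1.1³ = 998 and 750/0.9³ = 1029, against the printed 1000. Even if dropout had also been built into the per-condition number, 176/0.9³ = 241, not 250.

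**The case against.** - **The article is condensed.** The effect size metric, the test and any inflation factor may stand in a full protocol that is not shown. This is fair, and it is why the finding is limited to the printed figures: 250 does not follow from the inputs beside it. A fuller document could explain the figure but would not make the printed sentence consistent.
- **The gap does no harm to power.** This stands. On the printed inputs the trial has more women than it needs, which sets the severity.
- **250 is a Bonferroni figure.** A reader might infer that the authors divided .05 by the four primary outcomes, since .0125 gives 250 by the exact t-test. The text does not support this: it prints .05, mentions no correction, and 250 is a round number that a smaller effect size or a higher power reaches about as well.
- **A level of .0125 would settle multiplicity.** A reader might infer this too, but it goes too far. Dividing by four covers the outcomes only. The hypotheses also involve three between-arm contrasts (each intervention against control, and one intervention against the other), and there are three follow-ups.
- **The true power is 92%.** That figure holds only for a two-group comparison of means in which all women contribute to the outcome. The article says that each woman receives feedback on only two of the four behaviors (section Configuring intervention content and material), and it does not say how this enters the analysis. As an illustration only, if half of each condition were informative for a given outcome, n would be 125 and power at d = 0.3 about Φ(0.3/√(2/125) − 1.9600) = Φ(0.412) = 66%.

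**Conclusion.** The planning sentence is internally inconsistent. With a standardized mean difference of 0.3, 80% power and two-sided .05, about 175 to 176 women are needed per condition (525 to 528 in total), against the printed 250 (750). At 250 per condition and with all women contributing, power is about 92%, or the detectable effect at 80% power is about 0.25.

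The discrepancy is conservative, so it supports neither a claim that the trial is underpowered on its printed inputs nor a cut in the target. Which of the printed values is off cannot be told from the article. Severity is moderate: a figure that the trial relies on is stated wrongly, with no loss of power on the printed inputs.

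**What to change.** Keep recruitment unchanged. Restate the sentence with the test, the metric of the effect size, and values of n, effect size, power and per-comparison significance level that agree.

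- **If .05 applies to each comparison:** state that 250 per condition gives about 92% power for an effect size of 0.3, or 80% power for 0.25, and label this as a two-group calculation with all women contributing to the outcome.
- **If a corrected level was used for sizing:** print that level and use the same threshold in the analysis. If it is .05/4, add that it covers the four outcomes only, not the three between-arm contrasts or the three follow-ups.

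The authors need to check their own calculation to know which applies. The cost is a rewording of one sentence and no extra participants; under the second option the analysis section must carry the same threshold.

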#### Measurements

Measurement moments will be at baseline, one month, three months and nine months post-intervention, which is after participants have received the first two brochures of the intervention (see Fig. 6 for a flow-chart). A food frequency questionnaire based on validated measurement tools is used to measure the fruit, vegetable and snack intake [69–71]. An adapted version of the Short Questionnaire to Assess Health-enhancing Physical Activity (SQUASH) will be used to measure PA [72]. Furthermore, items measuring the sociocognitive determinants of dietary and PA behavior will be used (i.e. awareness of one’s own behavior, attitude, self-efficacy, social support and intention) which are based on previous studies and are adjusted to our target population [73–76]. The process will be evaluated by means of process variables used in previous research [77].

**Fig. 6 Fig6:**
[figure not shown]
Flow-chart of measurement moments and intervention procedure

#### Statistical analysis

Multivariable linear and logistic regression analysis will be conducted to assess group differences in the fruit, vegetable and snack intake and PA at different points in time. Moderation analysis will be conducted to assess whether the intervention effects are moderated by demographic factors, such as ethnic background or EI. Further, mediation analysis will be conducted to identify the factors that may explain the intervention effect (e.g. attitude and self-efficacy).

#### Ethical approval

This study was submitted to the committee for ethical evaluation of research at the Open University in Heerlen, the Netherlands (commissie Ethische Toetsing Onderzoek, cETO). According to the cETO, this RCT does not come under the WMO law (Wet maatschappelijke ondersteuning/Social support act). Therefore, ethical approval of the Regional Medical Ethics committee in the Netherlands was not necessary for this project. The RCT will, however, be conducted according to good research practice by informing participants about the study and by asking for their informed consent to participate. This study is registered with the Nederlands Trial Register (NTR: 4506).

## Discussion

The aim of this paper was to provide a detailed description of the development of two versions of a computer-tailored intervention aimed at improving dietary and PA behavior among Dutch, Turkish and Moroccan adult women living in the Netherlands. In the first version of the intervention, content matching is applied by tailoring to behavior and sociocognitive factors (e.g. awareness, attitude and self-efficacy). In the second version, the materials are additionally contextualized by tailoring the material to EI.

We used the intervention mapping (IM) protocol to develop a theory- and evidence-based intervention. IM has often been used to develop nutrition- and/or PA-improving interventions before, and was evaluated as a good and useful tool for systematically developing such interventions [78–80]. However, we encountered challenges during the intervention development process related to choosing determinants and methods for behavioral change among this specific target group. As little evidence is available regarding determinants of dietary and PA behavior for lower-educated and various ethnic groups, we cannot be sure that we chose the most important determinants. The same applies for the techniques we used in the intervention to initiate behavior change. These methods have not been tested among Turkish and Moroccan women in the Netherlands before. Preliminary research among our target group led us to make use of the same determinants and behavior change techniques, as the differences between the ethnic groups were minimal [30].

A further challenge in this project is to reach the lower-educated and ethnic-minority populations, since they have emerged as difficult target groups to recruit for scientific research [81]. Current interventions aimed at lower-educated and ethnic-minority populations are often implemented on a small scale. By making use of computer tailoring we developed an intervention that can reach large numbers of people, and still provide individual advice. This paper illustrates how intervention material can be contextualized using EI-tailoring and cultural appropriateness. EI-tailoring has been proven to be effective among African American populations in the U.S. [42]. A randomized controlled trial will show whether the interventions are effective among our specific target group and whether EI-tailoring is beneficial.
